**Clinical Trial Schedule**

| Items | Treatment and Observation Period | | | | | |
| --- | --- | --- | --- | --- | --- | --- |
| No. of Visits | Visit 1 | Visit 2^1)^ | | Visit 3 | Visit 4 | Visit 5 |
|  | Before surgery | Immediately after surgery | 7 days after surgery | 3 month after surgery | 6 months after surgery | 12 months after surgery |
| Visit Window (Day) |  |  | ± 2 | ± 14 | ± 14 | ± 30 |
| Inclusion/ Exclusion Criteria | ○ |  |  |  |  |  |
| Informed Consent | ○ |  |  |  |  |  |
| Basic Information and Medical History | ○ |  |  |  |  |  |
| Hematologic Tests^2)^ | ○ |  | ○ |  |  |  |
| Measurement of drainage volume^3)^ |  | ○ | ○ |  |  |  |
| Analysis of body composition | ○ |  |  | ○ | ○ | ○ |
| Investigational medical device prescription |  | ○ |  |  |  |  |
| Measurement in the range of shoulder joint’s motion | ○ |  |  | ○ | ○ | ○ |
| Evaluation on the upper limbs’ locomotive capacity | ○ |  |  | ○ | ○ | ○ |
| Evaluation of pain | ○ |  |  | ○ | ○ | ○ |
| Evaluation of Adverse Events |  |  | ○ | ○ | ○ | ○ |

1) The test for blood and the adverse events scheduled on the visit 2 will be evaluated based on the adverse events discovered on the discharge date of patient or on the 7th day subsequent to the surgery by revisiting the patient.

2) Hematologic Tests - WBC, Neutrophil

The blood test to be performed on the 7th day subsequent to surgery will be conducted only if the adverse events such as the flare onto the surgical site or the fever exists following the surgery. The intention of above-mentioned test (test item: CBC, CRP, and etc.) is to check whether the inflammation factor is increased and the number of white blood cell within 7 days from the surgery.

3) Measurement of drainage volume - Shall be measured at an interval of two days until the 7th day from the surgery date and complete the measurement of it on the discharge date from hospital.

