**11-3 Assessment of Safety Criteria and method**

(1) Laboratory Tests

Hematologic Tests – WBC, Neutrophil

(2) Evaluation of Adverse Events

Investigators shall educate the subject to report the adverse events voluntarily and occasionally and check the adverse events which occurs in the subject by interviewing or reviewing the report kept in hospital during the visit.

(3) The evaluation on pain derived from the movement

(4) Drainage volume subsequent to the surgery

Drainage volume (ml) unit shall be surveyed.

(5) Expected Adverse Events

In case of the infection which occurs as an adverse events following the use of investigational medical device, we confirmed its degree by checking up the clinical sign and performing the blood test (the white blood cell count (WBC)) scheduled to 7th following the surgery.
In case of the allergic reactions (generalized eruption, respiratory dyspnea, edema, pain, and inflammation), we analyzed the causal relationship with the usage of investigational device by checking up the clinical signs.

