**15-2 Safety Criteria Analysis**

(1) Adverse Events

All the AE that developed during the study period were analyzed. Their onset rate, the onset rate of AE that caused dropout, and the onset rate of SAE were summarized by group. They were coded using WHO-ART, then tested through the Chi-square test or Fisher’s exact test. The onset rates of AE were suggested as: onset rate of all adverse events, and the onset rate associated with the investigational device.

(2) Laboratory Tests

In the case of baseline continuous data from the laboratory test, descriptive statistics quantity (such as mean, SD, median, minimum, and maximum) was calculated, and their normal distribution was tested, then the difference between the groups was compared using One side, Two sample student t-test. In the case of categorical data, their descriptive statistics quantity (frequency and percentage) was suggested, and the difference between the groups was compared using the Chi-square test or Fisher’s exact test. After checking the investigational group’s test value came out on preoperative day and the 7th day following the surgery is different from it of control, we checked whether this difference is included within the normal error range or not.

1) Assessment of Criteria: Adverse events (Visit2, Visit3, Visit4, Visit5) and Hematologic Tests (Visit1, Visit2)

2) Evaluation criteria: The safety of investigational device is considered to be confirmed if the difference between the investigational group’s result value and control’s result value isn’t significant.

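### Section 15-2 counts preoperative (Visit 1) haematology among the criteria for declaring the device safe, although those values precede randomisation and device application (minor; the error is conservative)

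*Protocol*

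**What the plan says.** **Criteria and rule.** Protocol section 15-2 lists what enters the safety assessment: "Adverse events (Visit2, Visit3, Visit4, Visit5) and Hematologic Tests (Visit1, Visit2"). The rule follows directly: "The safety of investigational device is considered to be confirmed if the difference between the investigational group’s result value and control’s result value isn’t significant". No visit is exempted.

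**Laboratory method.** The same section opens its laboratory paragraph with "In the case of baseline continuous data from the laboratory test, descriptive statistics quantity", and for those data says that "the difference between the groups was compared using One side, Two sample student t-test". It then refers to whether the device group's "test value came out on preoperative day and the 7th day following the surgery is different from it of control", and adds that any difference is checked against a normal error range, which is not defined. Section 16-1 (2) repeats a between-group test on baseline laboratory data, there with an independent t-test or Wilcoxon's rank sum test.

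**Variables.** Section 11-3 (1) names two: "Hematologic Tests – WBC, Neutrophil".

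**Timing.** The Clinical Trial Schedule and section 11-4 place Visit 1 before surgery. Section 10.3 (1) assigns the group after the operation. Section 11-4 lists randomisation and device application under Visit 2.

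**The concern.** A safety verdict should rest on data that the device could have influenced. Visit 1 WBC and neutrophils are measured before the groups exist. If the randomisation is sound, any difference between the later groups at that visit is chance. Similar values at that visit are equally uninformative, because they would be similar whatever the device does afterwards.

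Visit 1 has one useful role in the laboratory assessment: it is the reference against which each patient's day-7 value is read. Section 15-2 does not give it that role. It lists Visit 1 beside Visit 2 as a criterion and describes a between-group comparison of baseline values. Adverse events start at Visit 2 in the same list, so haematology is the only route by which pre-device data enter the verdict.

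At stake is a modest chance that a harmless device is refused the safe label because of a preoperative imbalance, and a safety statement that appears to rest on more evidence than it does.

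**Working it through.** The protocol gives no figure for the operating characteristics of the safety rule, so there is none to reproduce. The sample-size result in section 8-3 (86 per arm, 96 after dropout) does not enter: with no true difference, the rejection probability of a valid test equals its alpha whatever the sample size.

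**Step 1: can the device affect Visit 1?**
- Visit 1: before surgery (Clinical Trial Schedule; section 11-4).
- Group assignment: after the operation (section 10.3 (1)).
- Device application: Visit 2 (section 11-4).

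It cannot. The device effect does not enter the Visit 1 data.

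**Step 2: is Visit 1 described as a reference or as a comparison?**
- For range of motion, DASH and pain, section 15-1 speaks of the period running from the preoperative day to each later visit.
- For laboratory values, section 15-2 has no such wording. It sets preoperative and day-7 values against control, and the paragraph that names the test concerns baseline data.

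**Step 3: how often would Visit 1 alone block the verdict for a harmless device?**

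Inputs:
- Two tests, WBC and neutrophils (section 11-3 (1)).
- Alpha for safety: not stated, so assumed. One value is one-sided 0.025, which pairs the one-sided test of section 15-2 with the significance level of section 8-3. The other is two-sided 0.05.
- Correlation ρ between the two test statistics: not stated. Assumed range 0 to 0.9.
- Combination rule: not stated. Assumed that every comparison must be non-significant.

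Formula: P(at least one significant) = 2α − P(both significant). At ρ = 0 this equals 1 − (1 − α)².

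- ρ = 0, one-sided 0.025: 1 − 0.975² = 0.0494.
- ρ = 0, two-sided 0.05: 1 − 0.95² = 0.0975.

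For ρ above 0, P(both significant) comes from the bivariate normal distribution:

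| ρ | one-sided 0.025 | two-sided 0.05 |
| --- | --- | --- |
| 0 | 4.9% | 9.8% |
| 0.7 | 0.050 − 0.0083 = 4.2% | 0.100 − 0.0165 = 8.3% |
| 0.9 | 0.050 − 0.0148 = 3.5% | 0.100 − 0.0296 = 7.0% |

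**Step 4: can Visit 1 hide harm?** Under the same all-must-pass assumption, a significant day-7 difference still blocks the verdict whatever Visit 1 shows. A non-significant Visit 1 adds a pass without content and offsets nothing. With Visit 1 removed from the rule, its contribution to wrongly withheld verdicts falls to 0.

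**The case against.** **The list may be only a collection schedule.** The visits named match the schedule table, and the rule speaks of one difference, in the singular. The comparison sentence names the preoperative day and day 7 together, so a pre/post comparison may have been meant. If the word baseline were taken to restrict the paragraph to Visit 1, day-7 values would have no stated test at all. This reading is possible. However, the text has none of the from-baseline phrasing that section 15-1 uses for efficacy, and a reader applying 15-2 as written would compare the arms at Visit 1. If a change was intended, the wording still needs correcting.

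**A further check is planned.** An observed difference is to be held against a normal error range. That may spare the device from a trivial Visit 1 imbalance. The range is undefined and its link to the significance rule is unclear, so it qualifies the figures without removing the problem.

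**Details may be left to an analysis plan.** Choosing between change and covariate adjustment often is. The criteria and the decision rule, however, are fixed in the protocol itself.

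**Two stronger readings are tempting and not supported.**
- A reader might infer that a balanced Visit 1 helps an unsafe device to pass. If all criteria must be non-significant, it does not. Dilution would need the results to be weighed together, which the protocol does not say.
- A reader might infer that Visit 1 is the only haematology comparison covering all patients, because a schedule footnote says the day-7 test "will be conducted only if the adverse events such as the flare onto the surgical site or the fever exists following the surgery". Sections 11-1 (4) and 11-4 (Visit 2) list the day-7 blood test without that condition. The protocol contradicts itself here, so the inference is not settled.

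**Conclusion.** The point holds in a limited form. As written, section 15-2 (2) brings into the safety verdict a comparison that cannot depend on the device, and does not confine Visit 1 to its role as the reference for day 7.

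The numerical effect is the 3.5–4.9% or 7.0–9.8% chance of a wrongly withheld verdict derived above. It rests on an assumed alpha, an assumed correlation range and an assumed all-must-pass rule. The check against a normal error range could lower it. The error runs in the conservative direction: it can cost a harmless device its favourable verdict but does not conceal a day-7 signal.

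Severity is minor. The primary endpoint, the sample size and the detection of harm are unaffected.

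**What to change.** In section 15-2 (2):
- Remove Visit 1 from the haematology entry in the list of safety criteria and from the significance rule.
- State that Visit 1 WBC and neutrophils are reported descriptively by group.
- Base the laboratory comparison on the day-7 value adjusted for the patient's Visit 1 value, or on the change from Visit 1, and reword the sentence on the preoperative day and day 7 to match.

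Align the laboratory text of section 16-1 (2), which also tests baseline values between groups.

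**Cost.** A wording change. Visit 1 values are already collected, so no new data or patients are needed. The one small drawback is that patients without a Visit 1 value need a simple rule.

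**Not resolved by this change.** Two separate matters remain. The schedule footnote (repeated in section 11-4) and the unconditional entries in sections 11-1 (4) and 11-4 (Visit 2) must be reconciled on who has a day-7 blood test. Taking non-significance as proof of safety is a weakness of the rule whichever visits enter it.

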**H_0_ : D ≤ 10 H_1_ : D〉10 (D=Experimental group(EG) ROM Mean – Control group(CG) ROM Mean)**

* Basis of Calculation: Assumptions for estimating the effective subject number.

① Significance level α = 0.025

② The EG estimation number is 1 time that of CG.

③ Type 2 error (β) is 0.1, and statistical power 90% is maintained.

④ The difference in the average value between two groups: 10 degree.

[figure not shown]

[figure not shown]

[figure not shown]

| Power | N1/N2 | Equivalence Margin  (E) | Actual  Difference  (D) | Significance  Level  (Alpha) | Beta | Standard  Deviation1  (SD1) | Standard  Deviation2  (SD2) |
| --- | --- | --- | --- | --- | --- | --- | --- |
| 0.90022 | 23/23 | 5 | 10 | 0.025 | 0.09978 | 5 | 5 |
| 0.80044 | 17/17 | 5 | 10 | 0.025 | 0.19956 | 5 | 5 |
| 0.90004 | 86/86 | 5 | 10 | 0.025 | 0.09996 | 10 | 10 |
| 0.80003 | 64/64 | 5 | 10 | 0.025 | 0.19997 | 10 | 10 |
| 0.90022 | 191/191 | 5 | 10 | 0.025 | 0.09978 | 15 | 15 |
| 0.80044 | 143/143 | 5 | 10 | 0.025 | 0.19956 | 15 | 15 |
| 0.91250 | 23/23 | 10 | 15 | 0.025 | 0.08750 | 5 | 5 |
| 0.80704 | 17/17 | 10 | 15 | 0.025 | 0.19296 | 5 | 5 |
| 0.90323 | 86/86 | 10 | 15 | 0.025 | 0.09677 | 10 | 10 |
| 0.80146 | 64/64 | 10 | 15 | 0.025 | 0.19854 | 10 | 10 |
| 0.90022 | 191/191 | 10 | 15 | 0.025 | 0.09978 | 15 | 15 |
| 0.80044 | 143/143 | 10 | 15 | 0.025 | 0.19956 | 15 | 15 |

Suppose that the 10% subject is dropped out in the middle of trial, the necessary total subject is 192 persons composing of 96 persons for the experimental group and 96 persons for the control.

| Target subject number | EG | CG | In total subject number |
| --- | --- | --- | --- |
| Subject number for final efficacy evaluation | 86 | 86 | 172 |
| Subject number in consideration of drop-out rate (10%) | 96 | 96 | 192 |

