**12-5 Expected adverse events during and after the surgery**

Bleeding, infection on wound, necrosis of skin flap, Reduction of shoulder joint’s movable range, annular syndrome on breast, seroma, nerve damage and paresthesia, lymphedema, pain and discomfort in neck, back, and arm, tightening feeling in the skin of surgical site

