**16. Assessment of Safety Criteria, and Evaluation and Side Effect Report (including adverse events)**

**16-1 Assessment of Safety Methods**

The adverse events confirmed at the physico-chemical exam or reported from the subject are included in the analysis for evaluating the occurrence rate of adverse events which occurred within the investigational group and control and its severity and its type.

(1) Adverse events

All the AE that developed during the study period were analyzed. Their onset rate, the onset rate of AE that caused dropout, and the onset rate of SAE were summarized by group. They were coded using WHO-ART, then tested through the Chi-square test or Fisher’s exact test. The onset rates of AE were suggested as: onset rate of all adverse events, and the onset rate associated with the investigational device.

(2) Laboratory Tests

In the case of baseline continuous data from the laboratory test, descriptive statistics quantity (such as mean, SD, median, minimum, and maximum) was calculated, and their normal distribution was tested, then the difference between the groups was compared using the independent t-test or Wilcoxon’s rank sum test. In the case of categorical data, their descriptive statistics quantity (frequency and percentage) was suggested, and the difference between the groups was compared using the Chi-square test or Fisher’s exact test.

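### Section 15-2 treats a non-significant difference between arms as confirmation of safety, in a trial sized only for range of motion and with no direction in the rule

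*Protocol*

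**What the plan says.** **Decision rule.** Protocol section 15-2 closes with its evaluation criterion: "The safety of investigational device is considered to be confirmed if the difference" between the device group and the control group is not significant. The rule covers "Adverse events (Visit2, Visit3, Visit4, Visit5) and Hematologic Tests (Visit1, Visit2").

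**Tests behind it.** For adverse events, section 15-2 says: "They were coded using WHO-ART, then tested through the Chi-square test" or Fisher's exact test. For continuous laboratory data it says "the difference between the groups was compared using One side, Two sample student t-test", naming no direction. Section 16-1 describes the same laboratory comparison differently: "the difference between the groups was compared using the independent t-test" or a Wilcoxon rank sum test.

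**Sizing.** Section 8-3 sizes the trial on range of motion: 86 evaluable per arm, raised for 10% dropout so that "the necessary total subject is 192 persons composing of 96 persons for the experimental group and 96 persons for the control". The protocol states no margin, significance level or power for safety. Section 15-3 lists a power of 80% without tying it to any endpoint.

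**Which events count.** Section 12-5 includes among the events expected from surgery "infection on wound, necrosis of skin flap, Reduction of shoulder joint" movement, lymphedema, and pain in the neck, back and arm. Section 12-4 lists pain among the events expected from the device, and section 11-3 lists pain on movement as a safety assessment.

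**Laboratory sampling.** Footnote 2 of the Clinical Trial Schedule, repeated in section 11-4, restricts the day-7 blood test to subjects with signs such as fever or a flare at the surgical site.

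**The concern.** A test that fails to reject equality may do so because the arms are alike or because the trial is too small to tell. The rule treats both cases as proof of safety, so fewer subjects or noisier data make safety easier to confirm. Evaluating safety is a stated aim (section 6-2) and the device is left in the surgical wound, so an unsupported formal safety conclusion matters.

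The rule also ignores which arm has more events. Reduced shoulder movement and pain are listed adverse events and are also outcomes the device is meant to improve (sections 7-1 and 14-1). If it works, the adverse event comparison could become significant in its favour, and the stated condition for confirming safety would not be met.

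This is not a detail left to an analysis plan. The protocol itself sets the criterion.

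**Working it through.** **1. The plan's own figure.** Inputs from section 8-3: margin 5 and true difference 10 (or 10 and 15), so a distance of 5; SD 10; one-sided alpha 0.025; power 90%. The noncentral t calculation gives power 0.8999 at 85 per arm and 0.9032 at 86. So 86 is right for that distance, and 86 / 0.90 = 95.6 rounds up to 96. The figure reproduces, but it concerns range of motion only.

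**2. Chance that the rule is met when the device does harm.** Inputs: 96 per arm (section 8-3), chi-square or Fisher's test (section 15-2). Assumptions, because the protocol gives none: the event rates and a two-sided 5% level. For control rate p_C and device rate p_D, by exact enumeration:

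P(not significant) = sum over i, j of Bin(i; 96, p_C) × Bin(j; 96, p_D) × [p-value(i, j) above 0.05]

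| Control vs device | Fisher: power / rule met | Chi-square (uncorrected): power / rule met |
|---|---|---|
| 5% vs 10% | 0.181 / 82% | 0.258 / 74% |
| 10% vs 20% | 0.425 / 57.5% | 0.498 / 50% |
| 20% vs 40% | 0.830 / 17% | 0.866 / 13% |

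With 86 per arm, 5% vs 10% meets the rule 84% (Fisher) or 77% (chi-square) of the time, and 10% vs 20% does so 62% or 55%. Each figure is for one comparison; the protocol does not say how several are combined.

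A concrete case: 0 of 96 control events against 5 of 96 device events gives Fisher p = 0.059, so the rule is met. It takes 6 of 96 to reach significance (p = 0.029).

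**3. The beneficial direction.** Chi-square has no direction and no one-sided Fisher test is stated, so the same enumeration applies. A true fall from 20% to 10% is significant with probability 42.5% (Fisher) or 50% (chi-square); from 30% to 15%, 66% or 71%. In those cases the criterion is not met although the device did better.

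**4. What the trial can show.** At an assumed true rate of 5% in each arm, the 95% interval for the risk difference has half-width 1.96 × √(2 × 0.05 × 0.95 / 96) = 0.062, about 6 percentage points. At 10% per arm it is 1.96 × √(2 × 0.10 × 0.90 / 96) = 0.085.

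**5. Laboratory values.** Section 15-2 has a one-sided t-test without direction; section 16-1 has an independent t-test or Wilcoxon test for the same data. Under the non-significance rule, the test and side chosen can decide the outcome. In addition, the day-7 comparison includes only subjects with symptoms: a smaller, selected group in which non-significance is easier to reach.

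**The case against.** **The rule says if, not only if.** A reader might infer that any real fall in adverse events would make the device fail on safety. The text does not go that far. It defines no failure outcome, and only a statistically significant reduction misses the criterion. What stands is narrower: such a reduction would not meet the only criterion given.

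**The size depends on assumed rates.** A reader might also infer that a device doubling wound infection would be passed with high probability whatever the base rate. The protocol gives no infection rate and no safety significance level. At 20% to 40% the rule would be met only 13 to 17% of the time, so very large harms would usually show. At lower rates the weakness remains.

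**Subjects are protected by other means.** Sections 16-3 to 16-7 provide for causality assessment, follow-up and expedited reporting, and section 15-2 already plans per-arm rates of all, device-related, serious and dropout-causing events. This is correct. The defect lies in the concluding inference, not in data collection or individual safeguards, and it does not touch the primary efficacy result.

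**The surgery list is not the device list.** Section 12-5 concerns surgery and section 12-4 the device. But section 15-2 analyses all adverse events, so both lists enter the comparison.

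**The laboratory mismatch is minor.** Agreed. Both sections attach the test to baseline data, and this is a wording conflict to reconcile.

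**Conclusion.** The point holds. Section 15-2 fixes a safety conclusion that its tests cannot support. With 96 per arm and an assumed two-sided 5% level, a doubling of one event meets the rule 74 to 82% of the time from an assumed 5%, about 50 to 57.5% from 10%, and 13 to 17% from 20%. That non-significance is not evidence of safety needs no assumption; only the size does.

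The missing direction is a second, weaker fault, because it relies on reading the sole stated criterion as the one that decides. It is less certain for laboratory values, where the test is one-sided with an unstated side. The documents do not support saying that the trial is blind to all harm, or that every improvement counts against the device.

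**What to change.** - Delete the criterion in section 15-2 that safety is confirmed when the difference is not significant.
- Keep the planned per-arm rates of all, device-related, serious and dropout-causing adverse events, and add infection. Report each with the device-minus-control risk difference and a two-sided 95% confidence interval.
- State the conclusion descriptively, as the excess risk that the interval does and does not exclude (about 6 percentage points either side of the estimate at an assumed 5% per arm), without claiming that safety is confirmed. An upper-limit rule with no stated margin would only replace one undefined rule with another.
- Keep pain and reduced motion in the safety reporting. Sections 11-3 and 12-4 treat pain as a safety measure and an expected device event, and once the criterion is gone a benefit can no longer work against the device.
- Use one two-sided laboratory method in sections 15-2 and 16-1, and note that day-7 blood values come from symptomatic subjects only.

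Cost: wording in two sections and no new data. The downside is that the trial can no longer claim from a p-value that safety is confirmed.
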